### Recruitment

Recruiting centres will screen LC waiting lists and gallbladder clinic lists for potentially eligible patients. Potential participants will also be identified from urgent inpatient and ambulatory care admissions and ward handovers. Eligible patients will be provided with study information and will have the opportunity to ask questions before being approached for their informed consent (see online supplemental material 1). Patients who feel they have had insufficient time to consider the study will be invited to take home a consent form and questionnaire pack (where applicable) and to complete and return them by post. Details of all patients approached for the study and reasons for non-participation will be documented.

10.1136/bmjopen-2020-044281.supp1Supplementary data

### Randomisation

Randomisation will be performed by an authorised member of the local research team using a secure internet-based system to ensure allocation concealment. The allocation will be computer generated and stratified by centre.

Participants will be randomised to MRCP or EM in a 1:2 ratio. This ratio has been selected to reflect current levels of MRCP provision (13%–26% of patients at low or moderate risk of CBD stones currently undergo MRCP).^7^

### Interventions

The study interventions are preoperative MRCP and EM.

Participants allocated to the MRCP group will have an MRCP before the date of their listed LC. The study will make no changes to the usual hospital radiology protocols used for MRCP and will not impose any timelines for the MRCP or any subsequent interventions. If a CBD stone is found on MRCP, surgeons can manage extraction according to their usual practice. The study does not stipulate removal of identified CBD stones, and any further interventions are at the discretion of the clinician. If an ERCP is requested, it will be performed as a separate inpatient procedure before admission for LC.

Participants allocated to EM will be listed for LC without any preoperative imaging. If MRCP is carried out, for example, due to a change in a participant’s clinical circumstances after randomisation, this will be documented as a crossover.

In both groups, intraoperative imaging will not be permitted unless there is an anatomical reason to do so, or if a CBD stone is found on MRCP. Any deviations from the protocol will be recorded and monitored.

### Data collection

Data will be collected by the local study team at baseline, before, during and after LC and at hospital discharge (table 1). Data collection will be from hospital records, including operative notes, and will include information on any pre-LC MRCP and ERCP and any intraoperative imaging. Data will either be collected onto a paper case report form and transcribed into a secure electronic study database or entered directly into the database. During phase 1, safety data will also be collected from hospital records 90 days post-LC by the local study team.

### Linkage to routine data

With consent, participant identifiers will be sent to NHS Digital and equivalent organisations for participants recruited outside of England. These organisations will match and extract pseudonymised data for these participants for all episodes of hospital care for a minimum of 18 months from the point of randomisation and for a period of 12 months prior to randomisation. The data will include inpatient and critical care episodes, accident and emergency department attendances, outpatient appointments, diagnostic imaging investigations and mortality.

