### Sample size

The sample size of 13 680 has been chosen to test the hypothesis that EM is non-inferior to MRCP with respect to the primary outcome. In estimating the sample size, we have considered the proportion of patients that would be expected to experience the primary outcome, as identified in the CholeS audit (5%–10%) and through exploration of HES data.^7^ This includes patients at high risk of CBD stones. The consensus among clinicians on the study team was that the non-inferiority margin should be set at 1.5%, that is, that the risk of the primary outcome with EM should not exceed 8.5% assuming a risk of 7% after MRCP. A study of 13 680 participants will provide 90% power to test the non-inferiority hypothesis for a 7% event risk with MRCP and 80% power to test the non-inferiority hypothesis for a higher event risk of 8.5%, assuming 2.5% one-sided statistical significance and a 1:2 allocation ratio (MRCP:EM). The 20% sample of participants providing HRQoL data will be stratified by centre. This sample of 2736 participants will have >90% power to detect a small effect size of 0.12 standard deviation between groups on the EQ-5D-5L questionnaire.

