### Statistical analysis

The study will be analysed on an intention-to-treat (ITT) basis, that is, outcomes will be analysed according to the allocated treatment pathway irrespective of future management and events, and every effort will be made to include all randomised participants. Non-adherence to the treatment allocation will be documented. The primary analysis will follow the Consolidated Standards of Reporting Trials guidelines for a non-inferiority study.^15^ An analysis according to treatment pathway followed will also be performed for the primary outcome. As recommended, both analyses will be considered when assessing whether the hypothesis is met.^16^ The primary outcome will be compared using survival methods to allow for censoring. For participants without a qualifying primary outcome event, they will be censored at the time the dataset was compiled. If more than one qualifying event occurs (eg, two hospital admissions for gallstone-related complications), time to the first event will be used. The frequency of each element of the primary outcome and reasons for admission, where applicable, will be described. Secondary outcomes will be compared using a mixed model for continuous outcomes or a generalised linear regression model for binary outcomes, adjusted for prerandomisation measures when available. For secondary outcomes measured at multiple time points, changes in treatment effect with time since randomisation will be assessed by adding a treatment by time interaction to the model and comparing models using a likelihood ratio test. Model fit will be assessed, and alternative models and/or transformations (eg, to induce normality) will be explored where appropriate. Sensitivity analyses using multiple imputation for missing data will be explored. Analyses will be adjusted for centre, and treatment differences will be reported with 95% confidence intervals.

A detailed analysis plan will be prepared. There is no intention to compare any outcomes between groups at the end of phase 1; only descriptive statistics about eligibility, recruitment and adherence will be summarised at this time to determine whether the study satisfies the progression criteria.

Exploratory analyses will include:

Relationship between number and size of stones seen on MRCP and patient outcome (cohort undergoing MRCP only).Relationship between stones removed under ERCP or not (eg, ‘necessary’ vs ‘unnecessary’ ERCP) and patient outcomes (cohort undergoing ERCP only).

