For the study results to be generalisable, we aim to recruit both patients classified as being at low and moderate risk of CBD stones. Low-risk patients are defined as those with bilirubin, ALT and ALP all within the normal range of their local Trust. As of 23 August 2020, 67% of randomised participants were classified as being at low risk and 33% as moderate risk.

Another major challenge will be obtaining routinely collected data from England, Wales, Northern Ireland and Scotland. Applications to obtain routinely collected data are complex and time consuming, and a different application process is required for each nation. The coordinating centre has considerable experience in completing these applications, but they must be successful and timely for the primary outcome to be determined and health economic analyses to be completed.

The primary outcome for the study is composed of three elements. The first will compare hospital admissions for treatment of gallstone complications in the 18 months after randomisation. The second and third elements will compare postoperative complications of LC and complications of ERCP. These two elements are important to measure, as there is evidence of increased rates of some complications (eg, biliary leakage) in patients with retained stones post-LC.^26^ This may have relevance to participants randomised to EM. It is also possible that participants are overtreated with MRCP, and any subsequent ERCP, and suffer avoidable complications. These elements will help inform study results and application in practice. The primary outcome will be reported both overall and by each individual element.

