### Ethics and dissemination

This study was reviewed and given a favourable opinion by Yorkshire & The Humber – South Yorkshire REC on the 10 December 2018 (REC reference: 18/YH/0358). Each participating centre is required to provide evidence of local confirmation of capacity and capability prior to starting recruitment to the study. Informed consent to participate will be obtained from all study participants. Participants have the right to withdraw from the study at any time and, if they do withdraw, will be treated according to standard local hospital procedures. Routine data will continue to be collected for withdrawn participants, unless the participant explicitly asks for this data collection to stop.

The study findings will be disseminated through peer-reviewed publications and international conferences and will be provided to study participants. A study specific Twitter account will be used to promote the study, provide updates on milestones and disseminate study findings. After study completion and reporting, the technical appendix, statistical code and dataset generated from the study will be available from the corresponding author on request. The request must include a specification of the data requested and justification for that request (ie, a statement of purpose for which the data are required). The data may not be released unless all Bristol Trials Centre and sponsor requirements are fulfilled (eg, protocol, sample size calculation, REC and Health Research Authority approval if appropriate, a collaboration arrangement in place between the sponsor and the external body).

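### Event-free participants are censored when the dataset is compiled, even if their routine-data coverage ended earlier or never began

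*Protocol article*

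**What the plan says.** Under Primary outcome, the protocol article ascertains the outcome by linking study data to Hospital Episode Statistics and mortality data, or to the equivalents outside England. Under Linkage to routine data, identifiers are sent with consent, and "These organisations will match and extract pseudonymised data for these participants for all episodes of hospital care", for at least 18 months after randomisation and for the 12 months before it.

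Three places bear on whether a given participant is actually observed:

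- Linkage needs consent and a successful match (Linkage to routine data).
- Under Ethics and dissemination: "Routine data will continue to be collected for withdrawn participants, unless the participant explicitly asks for this data collection to stop".
- The Discussion says that each of the four nations has its own application process and that the applications are demanding: "they must be successful and timely for the primary outcome to be determined".

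The Statistical analysis section then gives a single rule: "For participants without a qualifying primary outcome event, they will be censored at the time the dataset was compiled". It states no exception. The same section aims to include everyone randomised and says that multiple imputation will be explored as a sensitivity analysis, without tying it to the primary outcome.

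**The concern.** Censoring should fall on the last date at which an event could have been seen. Dataset compilation is that date only for participants whose linkage is complete and current. Someone who stops routine data collection at month 6 is unobserved from month 6, but the rule censors them later. Someone never matched has no qualifying event on record from routine data, so the rule, read literally, gives them event-free time up to compilation. National extracts may also end on different dates, which one compilation date would not respect.

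This matters more than usual because the hypothesis is non-inferiority and the Sample size section sets the margin on the absolute scale, 1.5 percentage points (7% against 8.5%). Unobserved people carried as event-free lower both observed risks. If loss is similar in the two arms, any real difference shrinks with them, which makes a true excess with EM harder to see. The trial is also open, so requests to stop data collection could differ by arm.

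**Working it through.** **Inputs.** From the Sample size section: 13,680 participants; "assuming 2.5% one-sided statistical significance and a 1:2 allocation ratio (MRCP:EM"), hence 4,560 MRCP and 9,120 EM; margin 1.5 points; "90% power to test the non-inferiority hypothesis for a 7% event risk with MRCP". The unobserved fraction u is not given anywhere, so it is an assumption, shown as a range.

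**Step 1: reproduce the plan's figure.** With unpooled variance and 7% in both arms,

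n(MRCP) = (1.960 + 1.282)² × (0.07×0.93 + 0.07×0.93/2) / 0.015² ≈ 4,560.

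Tripling gives about 13,680, as stated (13,683 if the arm size is first rounded up to 4,561). Power at 4,560 and 9,120 is 90.0%. The stated number is met with no inflation, so it contains no allowance for unlinked participants.

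**Step 2: the rule applied literally.** Suppose fractions u(M) and u(E) are unobserved throughout but kept as event-free. The observed risks are 7%×(1-u(M)) and 8.5%×(1-u(E)) when the true risks lie exactly at the margin. The chance of wrongly declaring non-inferiority is

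Φ((0.015 - observed difference)/SE - 1.96), with unpooled SE.

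| Unobserved, MRCP / EM | Observed risks | Observed difference (points) | One-sided error |
|---|---|---|---|
| 0 / 0 | 7.00% v 8.50% | 1.500 | 2.5% |
| 1% / 1% | 6.93% v 8.415% | 1.485 | 2.7% |
| 2% / 2% | 6.86% v 8.33% | 1.470 | 2.9% |
| 5% / 5% | 6.65% v 8.075% | 1.425 | 3.6% |
| 10% / 10% | 6.30% v 7.65% | 1.350 | 5.2% |
| 2% / 4% | 6.86% v 8.16% | 1.300 | 6.2% |
| 4% / 2% | 6.72% v 8.33% | 1.610 | 1.4% |

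For the 2% / 4% row: SE = 0.47 points, (1.5 - 1.3)/0.4715 = 0.424, and Φ(0.424 - 1.96) = 6.2%. Swapping the arms moves the observed difference above the margin, and the error falls to 1.4%.

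**Step 3: where there is no bias.** If the true risks are equal and loss is equal, both observed risks shrink alike and the difference stays at zero. On the hazard-ratio scale under proportional hazards, ln(1-0.085(1-u))/ln(1-0.07(1-u)) is 1.224 at u = 0 and 1.223 at u = 10%. The equal-loss effect therefore acts through the absolute margin.

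**Step 4: the alternative.** If the unobserved are left out instead (loss unrelated to outcome), the error stays at 2.5% for equal u. Power at 7% in both arms goes from 90.0% to 89.4% (u = 2%), 88.5% (5%) and 86.8% (10%).

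Steps 2 and 4 treat a person as unobserved for the whole period and none of their events as known from other sources. Partial coverage, or events recorded locally, would make the dilution smaller than shown.

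**The case against.** A reader might infer that the plan counts unlinked participants as successes and so tilts the trial towards non-inferiority. The document does not support that. It nowhere says that unlinked people are kept as event-free. The Discussion implies that without the data the outcome would be undetermined, and multiple imputation is mentioned. The censoring sentence can be read as covering only participants whose outcome was ascertained, and the compilation date could be taken separately for each national extract. Nor does the outcome rest on routine data alone: they are linked with study data, and local teams record operative, postoperative, MRCP and ERCP details, so some complications would be known without a match. Coding a whole nation with no data as event-free is implausible, so the 10% row should not be read as that scenario.

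The direction is not fixed either, as Steps 2 and 3 show, and the article specifies survival methods, under which a hazard ratio would barely move with equal loss. At 1% to 2% equal loss the error is 2.7% to 2.9%. Finally, a detailed analysis plan is promised, and routine collection continues after withdrawal by default.

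Most of this stands and limits the claim. It does not remove it. The article states a censoring rule, so this is not detail left for later: an analysis plan that handled the matter properly would have to depart from the published sentence. For a participant who stops data collection, the conflict between that sentence and the Ethics and dissemination section needs no assumption about linkage rates. Multiple imputation does not help while the rule, taken literally, leaves no primary outcome missing. Local data collection runs to hospital discharge, with safety data at 90 days after surgery described for phase 1, and does not cover 18 months of admissions. The absolute scale remains relevant, because the margin is set on it and the first objective is a difference in proportions.

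**Conclusion.** The point holds in a limited form. The single censoring date credits event-free time that was not observed for participants whose coverage ended before compilation, and the rule makes no exception for those never linked.

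The size is unknown, because no linkage or opt-out rate is given. With roughly equal loss, true risks at the margin and a test on the absolute difference, the one-sided error is 2.9% at 2% loss and 3.6% at 5%, against 2.5%. Unequal loss could take it either way: 6.2% with 2% MRCP and 4% EM, 1.4% with the arms reversed. There is no bias in the difference when true risks and loss are both equal. The correction is worth making because it is cheap and removes a dependence on linkage from the primary comparison, not because a large bias has been shown.

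**What to change.** In the Statistical analysis section, replace the censoring sentence with a rule to this effect: participants without a qualifying event are censored at the earlier of the date on which their routine data collection stopped at their request and the last date covered by their nation's extract. Participants never linked are treated as having a missing primary outcome, addressed in the planned multiple-imputation sensitivity analysis, and not as event-free to compilation. Report the numbers linked, never linked and stopped early, by arm and nation.

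The extract already requested allows the check. It covers 12 months before and at least 18 months after randomisation and includes outpatient and imaging records, so a patient listed for surgery who has no record at all is very probably unmatched.

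The costs are a small loss of effective sample size and power (90.0% to about 89.4% at 2% unlinked and 88.5% at 5%) and a main analysis that leaves out the never-linked despite the aim of including everyone randomised. That departure should be stated openly, with the imputation analysis showing how far the conclusion depends on it.

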### MRCP quality assurance

To address the challenge of MRCP technique varying across participating centres, images and reports for a random 10% sample of participants who receive an MRCP will be transferred for independent quality assurance review by consultant radiologists. The MRCP examinations will be assessed for the type of sequences performed, the diagnostic quality of the images and level of concordance with the hospital reports. These data will provide an overview of current NHS practice and the overall quality of MRCP examinations, as well as characterising variation in MRCP technique in study centres.

### Statistical analysis

The study will be analysed on an intention-to-treat (ITT) basis, that is, outcomes will be analysed according to the allocated treatment pathway irrespective of future management and events, and every effort will be made to include all randomised participants. Non-adherence to the treatment allocation will be documented. The primary analysis will follow the Consolidated Standards of Reporting Trials guidelines for a non-inferiority study.^15^ An analysis according to treatment pathway followed will also be performed for the primary outcome. As recommended, both analyses will be considered when assessing whether the hypothesis is met.^16^ The primary outcome will be compared using survival methods to allow for censoring. For participants without a qualifying primary outcome event, they will be censored at the time the dataset was compiled. If more than one qualifying event occurs (eg, two hospital admissions for gallstone-related complications), time to the first event will be used. The frequency of each element of the primary outcome and reasons for admission, where applicable, will be described. Secondary outcomes will be compared using a mixed model for continuous outcomes or a generalised linear regression model for binary outcomes, adjusted for prerandomisation measures when available. For secondary outcomes measured at multiple time points, changes in treatment effect with time since randomisation will be assessed by adding a treatment by time interaction to the model and comparing models using a likelihood ratio test. Model fit will be assessed, and alternative models and/or transformations (eg, to induce normality) will be explored where appropriate. Sensitivity analyses using multiple imputation for missing data will be explored. Analyses will be adjusted for centre, and treatment differences will be reported with 95% confidence intervals.

A detailed analysis plan will be prepared. There is no intention to compare any outcomes between groups at the end of phase 1; only descriptive statistics about eligibility, recruitment and adherence will be summarised at this time to determine whether the study satisfies the progression criteria.

Exploratory analyses will include:

Relationship between number and size of stones seen on MRCP and patient outcome (cohort undergoing MRCP only).Relationship between stones removed under ERCP or not (eg, ‘necessary’ vs ‘unnecessary’ ERCP) and patient outcomes (cohort undergoing ERCP only).

Subgroup analyses will evaluate the primary outcome in patients defined by characteristics. The main subgroup analysis will be in patients with low versus moderate risk of CBD stones, which will be defined following phase 1. This definition is expected to be a composite of baseline LFTs, baseline CBD diameter on USS and LC admission type (elective or urgent). Further subgroups will be defined:

Patients referred for elective surgery versus patients undergoing urgent surgery.Patients with normal LFTs at baseline (ie, low risk) versus patients with abnormal (outside of local Trust upper and/or lower normal limits) LFTs at baseline (ie, moderate risk).Patients with a history of pancreatitis versus patients with no history of pancreatitis.

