### Study population

The target population is adults (18 years or older) with symptomatic gallbladder disease, scheduled and fit for LC as an elective or urgent procedure who are at low or moderate risk of CBD stones. Low or moderate risk is defined as CBD diameter ≤8 mm on ultrasound scan (USS), bilirubin ≤50 µmol/L and alanine transferase (ALT) less than three times the upper limit of normal (≤3 ×ULN) and/or alkaline phosphatase (ALP) ≤3 ×ULN. If the CBD cannot be visualised on USS, the patient may be recruited if no intrahepatic duct dilatation is reported.

Patients are excluded if they are unable to undergo MRCP, have evidence of empyema or perforated gallbladder requiring urgent intervention, have had a previous gastric bypass, have had a previous MRCP or endoscopic USS within the last 3 months, have had any previous ERCP or have haemolytic disease. Patients must be willing to participate in follow-up and be able to provide informed consent.

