## Discussion

The main challenge facing the Sunflower Study is the recruitment target of 13 680 participants. Recruitment started 1 month later than planned in January 2019. The initial focus was to open centres to recruitment, with a target of 36 centres recruiting within phase 1. The study has already exceeded this target. As of 23 August 2020, 48 centres were open to recruitment, and 2040 participants had been randomised. The QRI will be key to optimising recruitment, providing training at investigators meetings and recruitment tips for staff at participating centres.^23 24^ With a 48-month recruitment period, it will also be key for the study to keep centres engaged. Initiatives include the use of an active Twitter account, regular recruitment updates and centre targeted emails, biannual newsletters and annual investigators’ meetings. It will also be important to remain aware of other relevant research that could impact on the study. The study team will undertake annual literature reviews.

The study includes patients who are scheduled for LC as either an elective or urgent procedure. It is important to ensure that both pathways are represented to promote generalisability of the study results, but it is recognised that recruitment of urgent patients is challenging. These patients can be admitted at any time of day and over weekends when research nurses may not be available to approach patients and receive consent. As of 23 August 2020, 77.8% of randomised participants were elective referrals and 22.2% were from urgent admissions. The study is keen to involve surgical trainees in the recruitment process and is participating in the National Institute for Health Research associate Principal Investigator scheme.^25^ During study training, the local team is encouraged to consider recruitment from the urgent pathway, and the ratio of elective to urgent patients recruited is being monitored. The study feels that surgical trainees will be critical to the successful recruitment of urgent patients. Discussions from an investigator meeting identified that the inclusion criterion, ALT and/or ALP less than 2 ×ULN, was disproportionally excluding urgent patients, and so this was amended to 3× ULN. The impact of this amendment will be monitored.

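### The LFT subgroup counts values below the lower limit as moderate risk, and the elective/urgent split is not tied to a pre-randomisation time point

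*Protocol article*

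**What the plan says.** All of this is in the Protocol article.

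- **Main subgroup (Statistical analysis).** "The main subgroup analysis will be in patients with low versus moderate risk of CBD stones, which will be defined following phase 1". On its content: "This definition is expected to be a composite of baseline LFTs, baseline CBD diameter on USS and LC admission type (elective or urgent"). Two of the three components carry the word baseline; admission type does not.
- **Further subgroup, pathway (same section).** "Patients referred for elective surgery versus patients undergoing urgent surgery".
- **Further subgroup, LFTs (same section).** Normal LFTs are labelled low risk and are compared with "abnormal (outside of local Trust upper and/or lower normal limits) LFTs at baseline (ie, moderate risk").
- **Discussion.** "Low-risk patients are defined as those with bilirubin, ALT and ALP all within the normal range of their local Trust", with the result so far that "67% of randomised participants were classified as being at low risk and 33% as moderate risk".
- **Pathway at recruitment.** Study population describes patients "scheduled and fit for LC as an elective or urgent procedure who are at low or moderate risk of CBD stones", and the Discussion reports that "77.8% of randomised participants were elective referrals and 22.2% were from urgent admissions".

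**The concern.** There are three faults of definition.

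1. **Low values labelled as higher risk.** Every limit used in Study population to mark low or moderate risk of CBD stones is a ceiling. The LFT subgroup adds a floor and gives no reason for it. The Discussion's requirement that all three tests lie within range has the same effect. Participants with a low value and nothing raised would join the moderate group and pull its result towards that of the low-risk group.

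2. **Elective and urgent fixed at different times.** Referral is settled before randomisation; the surgery a person undergoes is settled later. Someone referred electively who ends up having urgent surgery fits both descriptions. The Introduction says that MRCP can delay the operation and that this can lead to more gallstone problems, and admission for such a problem is a primary outcome event. Actual admission type could therefore be related to both allocation and outcome. Participants who never have the operation, whom the Safety section foresees, would have no actual admission type at all.

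3. **One pair of labels, two definitions.** Low and moderate risk mean an LFT-only split in one place and a composite still to be settled in another. A participant could be low on one and moderate on the other.

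At stake is how the subgroup results can be read, not the main non-inferiority conclusion.

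**Working it through.** The article gives no figure for this point. The only design figure used below is the total of 13 680, and it reproduces: with 7% risk in both groups, a 1.5-point margin, one-sided 2.5%, 90% power and 1:2 allocation, the MRCP group needs 0.07 × 0.93 × 1.5 × (1.960 + 1.282)² / 0.015² ≈ 4561, and 3 × 4561 = 13 683.

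**A. The lower-limit rule**

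The limits in Study population are CBD diameter ≤8 mm, bilirubin ≤50 µmol/L, and ALT and/or ALP ≤3 × ULN. All are upper limits. The subgroup rule counts either side.

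Assumptions not in the document: 2.5% of values fall below the lower limit for each test that has one; tests are independent; *k* of the three tests (bilirubin, ALT, ALP) have a lower limit locally; the reported 67%/33% split used the within-range rule, lower limits included, and holds to the end.

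- Share of otherwise normal participants moved: 1 − 0.975^k.
- The 67% are those left after the move, so an upper-limit-only rule would give 0.67 / 0.975^k. Moved, as a share of all participants: 0.67 / 0.975^k − 0.67.
- As a share of the moderate group, *w*: divide by 0.33.

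| k | Otherwise normal participants moved | Share of all | Share of moderate group (w) |
|---|---|---|---|
| 1 | 2.5% | 1.7% | 5.2% |
| 2 | 4.9% | 3.5% | 10.5% |
| 3 | 7.3% | 5.3% | 16.0% |

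If those moved respond like the low-risk group, the moderate-minus-low contrast in treatment effect is multiplied by (1 − w): 0.95, 0.89 or 0.84. Positive correlation between the tests brings the k = 3 row closer to the first.

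For scale, at 13 680 the current split gives 9166 low and 4514 moderate. At 7% risk the 95% half-width of a risk difference is 1.96 × √(0.07 × 0.93 × 4.5 / n), which is 1.11 and 1.58 points. For the contrast between the two subgroups it is √(1.11² + 1.58²) ≈ 1.9 points. Sixteen per cent of a contrast of, say, 1.5 points is 0.24 points, which is small against that uncertainty but avoidable.

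**B. The elective/urgent split**

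This illustration applies only if actual admission type were used. The pathway shares, 77.8% and 22.2%, come from the Discussion. The rest is assumed: no true treatment effect; a fraction *e* of elective referrals would become urgent if allocated MRCP and not if allocated expectant management (EM); event risk is 20% in those people in either arm, 5% in other elective referrals and 12% in urgent ones.

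- Elective, EM minus MRCP: [0.05(1 − e) + 0.20e] − 0.05 = 0.15e.
- Urgent, EM minus MRCP: 0.12 − (0.12 × 0.222 + 0.20 × 0.778e) / (0.222 + 0.778e).

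| e | Elective difference | Urgent difference |
|---|---|---|
| 1% | +0.15 points | −0.3 points |
| 5% | +0.75 points | −1.2 points |

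The true difference is zero, and the margin is 1.5 points. Grouping by pathway at randomisation gives zero in both subgroups.

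**The case against.** The strongest reply concerns the second fault. The article never says that actual admission type will be used. Eligibility rests on how the patient is scheduled, recruitment draws on waiting lists and on urgent admissions, and the Discussion already sorts every randomised participant by pathway while recruitment continues. The likely intention is a baseline variable, loosely described. That stands: a reader might infer that the plan conditions on a post-randomisation variable, but the documents do not establish it. The bias in part B also needs people who switch to have the operation as urgent cases, which is not stated either.

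Second, the elective/urgent bullet and the lower-limit rule belong to the further subgroups. The composite for the main subgroup is only expected, and no LFT cut-off is given for it. A reader might infer that the main subgroup result will be biased or misclassified; the text does not support that.

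Third, leaving the composite until after phase 1 is disclosed, a detailed analysis plan is promised, and no comparison of outcomes between groups is intended at that stage. Deferral is therefore not in itself an error. The two LFT-only definitions also agree with each other; the clash is only that they share labels with the composite.

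Fourth, the 7% rests on assumed inputs, and the resulting dilution is modest. That is fair. It does not remove the fault, because the lower-limit rule is stated outright and nothing in the article justifies it.

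**Conclusion.** The concern holds in limited form. The firmest part is the lower-limit rule: followed as written, it places some participants with no raised LFT in the moderate group and weakens the low-versus-moderate contrast. Up to about 7% of otherwise normal participants would move if three independent tests each had 2.5% of values below the lower limit; fewer would move if some tests have no lower limit or the tests are correlated. Whether the rule reaches the main subgroup depends on how LFTs enter the composite, which is not yet stated.

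The elective/urgent wording is inconsistent in time, and admission type in the composite has no stated time point. This becomes a bias only if actual admission type is used, and its size then depends wholly on assumed switching rates and risks. The shared low/moderate labels are a naming conflict. The primary non-inferiority analysis in the whole population is not affected.

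**What to change.** Make three changes to the subgroup text and carry them into the analysis plan:

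1. For the LFT subgroup, count a test as abnormal only when it is above the local upper limit, and align the Discussion's definition. This concerns classification for analysis only, not eligibility or care.
2. Define elective and urgent by the pathway recorded before randomisation, both in the pathway subgroup and as a component of the composite. Every randomised participant then falls in exactly one group, including those who never have the operation.
3. Keep low and moderate risk for the composite and give the LFT-only split another name, such as LFTs not raised versus raised.

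The cost is wording. The Discussion's figures show that pathway and LFT status are already classified for randomised participants. The 67%/33% split would need to be recounted under the revised LFT rule.
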